## Methods

### Design and settings

A quasi-experimental cluster controlled trial was undertaken to evaluate an ICT-based intervention over 6 months, i.e., the PEGASO System, to promote healthy habits among adolescents. This study includes adolescents of 12 schools from four sites: England (UK), Scotland (UK), Lombardy (Italy) and Catalonia (Spain).

The target sample size of 525 with 2:1 allocation (intervention: control) was designed to be large enough in each school to be reasonably sure that large scale recruitment was possible, to have a representation from different socioeconomic groups, to allow for attrition and to give some indication of variance in the various proposed outcome measures which would permit a sample size calculation for a future cluster randomized controlled trial.

Ethical approval was granted by the clinical research ethics committee (CEIC) of all four intervention sites: South East Scotland Research Ethics Committee in the UK, Istituto di Ricovero e Cura a Carattere Scientifico (IRCCS) Policlinico of Milan in Italy and CEIC of Institut d’Investigació en Atenció Primaria de Salut Jordi Gol (IDIAP Jordi Gol) in Spain.

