### Analysis plan and statistical analysis

The analysis plan will include a description of all data at every assessment point and an overall comparison of baseline characteristics between intervention group (IG) and comparison group (CG), as well as by sites and gender. Knowledge/awareness, lifestyles and anthropometric measurements will be compared at pre and post intervention (month 6) utilising an intention-to-treat (ITT) approach, independently from drop-outs and non-adherence. Relevant changes among lifestyles and knowledge will be defined according to current recommendations from international guidelines [46]. The effect of the intervention could be modified by gender, cultural and socioeconomic level, body mass index (BMI), as well as by the baseline lifestyles, which will be controlled in the analysis. Changes in motivation will be assessed in the four assessment points and compared to baseline. For the intervention group, the results from SUS, EMO, satisfaction, trust and reputation questionnaires will be compared from month 4 to month 6. The level of engagement in the PEGASO platform will be assessed from indicators of usage at individual level, such as the number of days of interactions with the APPs or the daily number of steps, stored in the cloud.

Results will be reported as mean ± standard deviation (or median, percentile 25 and 75) for quantitative variables or frequency and percentage distribution for qualitative variables. Quantitative variables will be tested for normality, log-transformed if needed, and accordingly analysed with parametric or non-parametric methods. Chi-squared test will be used to analyse the association between independent qualitative variables, along with the McNemar test for paired samples. The Student t-test will be used for the comparison of means between two groups, and the paired t-test will be applied to assess changes within one same group. Alternatively, the corresponding nonparametric tests will be used, as required. The relationship between quantitative variables will be analysed using Pearson’s correlation coefficient or Spearman coefficient in the case of asymmetrically distributed variables. Techniques of principal component analysis (PCA) will be applied to identify patterns of variables best explaining outcomes of interest.

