Multivariate linear regression analysis and logistic regression analysis will be used to analyse the variables determining the changes in physical activity and eating and sleeping habits. In order to analyse the effect of the intervention, comparison will be made of the changes observed in the CG versus the IG, with estimation of the Cohen d statistic, adjusting for the variables that may influence the results.

The level of statistical significance will be set at α = 0.05 and all tests will be two-tailed. Statistical analyses will be carried out using the software packages SPSS, version 22.0 (SPSS Inc., Chicago, IL) and Stata (StataCorp. 2009. Stata Statistical Software: Release 11. College Station, TX: StataCorp LP). Focus groups will analysis will be done with the support of Atlas. Ti /NVIVO and by triangulation of analyst.

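### The equal-variance Student t-test is named for 2:1 non-randomised arms, so its 5% level is unprotected if the arm SDs differ; the Welch test is a free safeguard

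*Protocol article*

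**What the plan says.** Under Analysis plan and statistical analysis, the article names the test: "The Student t-test will be used for the comparison of means between two groups". The only fallback is "Alternatively, the corresponding nonparametric tests will be used, as required", which follows a check of normality and possible log-transformation. Unequal variance is not mentioned. The error rate is fixed in the same section: "The level of statistical significance will be set at α = 0.05 and all tests will be two-tailed".

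Design and settings gives a target of 525 pupils at 2:1, intervention to control. No power, effect size or SD lies behind that number; one of its stated purposes is "to give some indication of variance in the various proposed outcome measures". The design is quasi-experimental. Under Recruitment and group allocation, schools were approached through researchers' contacts. Both arms were formed from whole classes at two sites; elsewhere they were formed from early-responding volunteers, with the comparison pupils coming from another school.

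On effect variation the article says: "The effect of the intervention could be modified by gender, cultural and socioeconomic level", and also by BMI, "as well as by the baseline lifestyles, which will be controlled in the analysis". The intervention effect is then to be analysed as change in one group against the other, covariate-adjusted, with Cohen d.

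**The concern.** The Student t-test pools the two variances, weighting each arm by its size. With equal arms this hardly matters, because the pooled standard error stays close to the true one even if the SDs differ. With 2:1 arms the pooled variance follows the larger arm, whereas the true standard error depends more on the smaller one. If the larger arm is more variable, the standard error is overstated: intervals are too wide and power is lost. If the smaller arm is more variable, it is understated: intervals are too narrow and false positives exceed 5%.

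Randomisation would make the arms alike in spread when the intervention does nothing. Here there is none, so the SDs can differ even under no effect. Ordinary linear regression of change assumes one residual variance and has the same sensitivity. Adjusting for the main effect of a covariate does not remove variation in the effect across that covariate.

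**Working it through.** **Inputs from the article.** N = 525 at 2:1, so 525 × 2/3 = 350 intervention and 525/3 = 175 comparison. Two-sided α = 0.05.

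**Assumed inputs.** The ratio of the arm SDs, since the article gives no SD. Pupils are treated as independent, to separate this issue from clustering.

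**Formulas.** With s₁ the intervention SD and s₂ the comparison SD:

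- true variance of the difference: V_true = s₁²/350 + s₂²/175
- variance used by the test: V_pooled = s_p² × (1/350 + 1/175), where s_p² = (349 s₁² + 174 s₂²)/523
- true level = 2 × [1 − Φ(1.96 × √(V_pooled/V_true))]

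**The plan's own figure.** With equal SDs, V_pooled = V_true and the level is 0.0500, as stated.

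**Worked case, intervention SD 1.3 times the comparison SD.** s_p² = (349 × 1.69 + 174)/523 = 1.460. V_pooled = 1.460 × 0.008571 = 0.01252. V_true = 1.69/350 + 1/175 = 0.01054. The SE ratio is √1.187 = 1.090, so the level is 2 × [1 − Φ(2.136)] = 0.033.

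**Worked case, comparison SD 1.3 times the intervention SD.** s_p² = (349 + 174 × 1.69)/523 = 1.230. V_pooled = 0.01054. V_true = 1/350 + 1.69/175 = 0.01251. The SE ratio is √0.842 = 0.918, so the level is 2 × [1 − Φ(1.799)] = 0.072.

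| Assumed SD ratio | Intervention arm more variable: SE ratio, level | Comparison arm more variable: SE ratio, level |
|---|---|---|
| 1.12 | 1.038, 4.2% | 0.964, 5.9% |
| 1.3 | 1.090, 3.3% | 0.918, 7.2% |
| 1.5 | 1.138, 2.6% | 0.879, 8.5% |

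At a fixed 2:1 split the variance ratio V_pooled/V_true is close to (2r + 1)/(r + 2), with r = s₁²/s₂². It does not depend on N, so attrition that leaves the 2:1 ratio intact neither helps nor hurts. In a 1:1 design of the same total (262 and 263) the level stays between 0.0498 and 0.0502 for SD ratios from 0.67 to 1.5.

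**Which direction is likelier.** If effects vary between pupils independently of the untreated outcome, the intervention variance grows. An effect SD of half a comparison SD gives r = 1 + 0.25 = 1.25, an SD ratio of 1.12 and a level of 4.2%. Smaller effect SDs of 0.2 and 0.3 give 4.85% and 4.68%. If pupils with worse untreated outcomes gain more, the intervention arm can become less variable. With an assumed correlation of −0.5 and an effect SD of 0.2, r = 1 + 0.04 − 0.20 = 0.84 and the level is 5.7%. With an effect SD of 0.5, r = 1 + 0.25 − 0.50 = 0.75 and the level is 6.2%.

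**With the Welch test.** In 40,000 simulated trials per scenario at 350/175, intervention-to-comparison SD ratios of 0.67, 0.8, 1, 1.25 and 1.5 gave Welch levels of 4.98%, 5.12%, 5.10%, 5.01% and 5.01%. The pooled test gave 8.34%, 7.02%, 5.07%, 3.47% and 2.62%. The simulation error is about √(0.05 × 0.95/40,000) = 0.11 percentage points.

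**The case against.** The strongest reply is that nothing in the article is shown to be wrong. It gives no SDs, and with equal SDs the level is exactly 5%. It never uses the word pooled, and the form of the t-test is a detail that an analysis plan could settle. The study is sized for feasibility, the adjusted comparison of changes stands beside the bare t-test, and clustering probably distorts the level more.

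Most of this stands. The part that does not is the claim of silence. A test is named, its usual meaning is the equal-variance form, and the only alternative offered deals with non-normality.

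Three stronger readings are tempting, and the documents do not support them:

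- **That the stated 5% does not hold.** This would need unequal arm SDs, and no passage reports or predicts them.
- **That the plan expects the effect to vary and so forecasts inflated error.** The article says only that the effect could be modified by listed covariates, which it intends to control. If there is no effect there is nothing to vary. If effects do vary, the usual result is a conservative test.
- **That recruiting volunteers in some places and whole classes in others makes the comparison arm more variable.** Under Recruitment and group allocation, each strategy was applied to both arms. It separates sites, not arms, and gives no reason for a larger comparison SD.

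The article also does not say that Cohen d will use a pooled SD, so no fault can be charged there.

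**Conclusion.** The point holds as a modest, cost-free improvement and not as a wrong figure. The named test leaves its 5% level unprotected at 350/175 with arms that were not randomised. Under assumed SD ratios of 1.12 to 1.3 the true level would be about 3.3% to 4.2% if the intervention arm is more variable, and about 5.9% to 7.2% if the comparison arm is. The first direction is the one that varying effects would usually produce, and its cost is power and interval width, not false positives. These figures rest on the assumed ratios, independent pupils, a large-sample approximation and the planned 2:1 split.

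For scale, take 12 schools of about 525/12 ≈ 44 pupils and an assumed intraclass correlation of 0.01 to 0.05. The design effect 1 + (43.75 − 1) × ICC is then 1.43 to 3.14, and an analysis that ignores clustering would have a level of roughly 10% to 27%. That is a separate issue with its own correction, and changing the t-test does not help with it.

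**What to change.** In Analysis plan and statistical analysis, replace the Student t-test with the Welch (unequal-variance) t-test for all between-arm comparisons of means. Add that the linear models of change will use heteroscedasticity-robust standard errors. The paired within-group tests need no change.

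This costs one sentence. Both software packages named in the article offer the test. When the SDs are equal, the two tests behave almost identically at these sizes (simulated levels 5.07% and 5.10%).

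If the models are revised to allow for class or school, cluster-robust standard errors would cover unequal variances as well and would replace the robust errors proposed here. With only 12 schools they would need a small-sample correction.

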## Discussion

In general, and in the field of health and medicine in particular, in recent years information and communication technologies have experienced rapid growth. Some authors point out that the use of the internet and associated technologies such as computer apps represent a revolution within the medical field, since they are fast, versatile, manageable, illustrative tools that allow people to be empowered with their health [47]. However, this vast development of health apps and those related with healthy lifestyles promotion are not encompassed by clear and sufficient scientific evidence on health improvement. For instance, two recent systematic reviews concluded that mobile phone interventions can diminish sleep disorders and to enhance sleep quality [48] and mobile phone app-based interventions may be useful tools for weight loss [49]. However, some other reviews showed modest evidence on the efficacy of intervention based on health apps on the promotion of healthy habits related with diet, physical activity and sedentary behaviour in children and adults [50] or in improving preventive behaviours among adolescents [51, 52]. Schoeppe and collaborators concluded in their systematic reviews that multi-component interventions appear to be more effective than stand-alone app interventions [50]. In this sense, the PEGASO system could be considered as multi-component intervention, which includes several apps, a game and smart sensors, and which targets multiple health behaviours All the reviews highlighted the necessity to a) involve end-users on the development of app-based interventions and b) evaluate the health effects of app-based interventions by conducting experimental studies to obtain sufficient scientific evidence [48–51].

The first part of the PEGASO F4F study developed a multi-dimensional ICT based intervention that includes the use of smartphone applications, a game and the use of wearables to promote healthy habits among adolescents. An iterative pre- trial study has already been undertaken to achieve the user centred design approach of PEGASO F4F. The aim of this was to increase the likelihood that the system will meet the requirements of teenagers and be accepted by this specific group of end users. Volunteers from the 4 sites tested the platform in different moments of the development in an iterative process. Their feedback was used to assess user interaction and experience, usability and the security and confidentiality requirements of the PEGASO system.

The present study aims to test the methodology to investigate the effectiveness that the use of the Pegaso system will have on teenage health awareness and the improvement of healthy habits with regards to adherence to recommendations and habit formation in terms of dietary behaviour, physical activity and sedentary and sleeping behaviour among adolescents.

Moreover, the present study will assess the user experience through validated questionnaires and focus groups in order to receive feedback from end users when they are introduced to the new technology, over a short-term period of use and then also over a longer period of time, 6 months after set up. The purpose of this is to understand how teenagers utilize proactive mHealth systems over time, understand the relationship between UX and health behaviours/ habit formation, and provide points of learning for industry looking to develop health ICT’s and other interventions for young people; specifically adolescents.

The study follows most of the recommendations of the CONSORT for quasi experimental studies [53]; however, participants are not be blinded to the intervention due to the nature of the intervention. Self-reported data is used to measure main results related to healthy habits modification and knowledge. These are assessed through the validated questionnaires selected for this trial.

According to the availability of each site, two approaches for the selection of comparative groups were foreseen; the comparative group either came from the same school or from a different school. Both, clustered and non-clustered quasi-experimental studies have their own advantages and disadvantages. A possible cross-over effects regarding the fact that both intervention and comparative groups are from the same schools may occur; social peer influence can be strongly associated to lifestyles and influence the results of the comparative group. However, we believe that adolescents tend to mainly interrelate with mates from their same class. Moreover, PEGASO F4F is not a school-based intervention itself; on the contrary, it was conceived as an individual intervention with several social components. By having both approaches it can provide us with some insight regarding the role of the social component and the impact if may have on the intervention.

The results of this study target improvements on dietary habits, physical activity and sedentary time and sleep quality among adolescents. Specifically results could lead to:
improvement in adolescent lifestyles (in terms of awareness, adherence and habit formation)improved knowledge among adolescents about health and wellbeing and the impact of their personal day to day decisions on their healthan appreciation of how new technologies based on mHealth can assist them in their lifestyle choices and promote positive health behaviours.Improved teenage mHealth interventions that are more appropriately designed to meet the specific needs of these young users

Positive results from this ICT based multi component intervention may represent an opportunity and influential tool against the development of chronic disease during adulthood.

## Data Availability

Not applicable.

## Abbreviations

App: Informatics application
BMI: Body Mass Index
EMO: Emotional Metric Outcomes
ICT: Information and Communication Technologies
mHealth: Mobile Health
PAQ-A: Physical Activity Questionnaire for Adolescents
PEGASO: Personalised Guidance Services for Optimising lifestyle in teen-agers through awareness, motivation and engagement
SHS: Sleep Habits Survey
SSBQ: Screen time-based sedentary behaviour questionnaire
SUS: System Usability Scale
UX: User Experience
